### Trial design {8}

This study will be a multi-center, prospective, randomized patient-blind controlled trial and employ a between-subject, pre- and post-tests design with a treatment and control group. It has been designed to be a superiority trial assessing motivational interviewing compared to standard audiological care. The SPIRIT (Standard Protocol Items: Recommendations for Interventional Trials) reporting guidelines were used to develop the methodology.

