### Sample size {14}

Aazh et al.’s [6] feasibility investigation of assessing HA data-logged hours of use in response to MI concluded that a standardized difference of 0.6 was best for sample size estimation. Therefore to discern this difference or greater at a 5% significance level with a power of 80%, 45 patients will be required in each intervention arm based on Machin and Campbell’s [21] clinical trial design tables. Therefore, 90 participants in total at a randomization ratio of 1:1.

An allowance of 50% participant dropout rate was adopted in this study as opposed to the 20% drop out identified by Aazh et al. to compensate for the uncertainties or anticipated higher drop rate due to the COVID-19 pandemic [6]. This higher rate is reasonable because a previous hearing aid RCT trial conducted by our senior investigators who recruited participants from audiology clinics within the greater Vancouver area, in part over the pandemic period with 3 months’ follow-up, resulted in 39.1% of participant data in the intervention arm being unavailable because of participants’ failure to attend follow-up or complete study questionnaires fully [24]. This leads to an adjusted sample size of 180 participants, 90 per group.

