### Interim analyses {21b}

Initial interim analysis will be performed when 30% of the participant recruitment is achieved to determine that the intake characteristics (age, sex, and degree of hearing loss) are similar in both arms. A second interim analysis will be performed when 50% of the recruited participants’ follow-up data is available to determine if a difference is evident in the outcomes. The results will guide the decision to continue the study.

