## Oversight and monitoring

### Composition of the coordinating center and trial steering committee {5d}

The coordinating center and trial steering group (TSC) will consist of PI, study co-ordinator, and a research assistant.

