### Composition of the data monitoring committee, its role, and reporting structure {21a}

A data monitoring committee is not needed over the course of this study as there is a low risk of adverse events.

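### A between-arm outcome look at half of follow-up feeds the decision to continue, with an ambiguous criterion and no boundary in this protocol, so neither the stated 5% nor the 80% is assured

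*Protocol article*

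**What the plan says.** The protocol article, Interim analyses {21b}, describes two looks. The first, at 30% of recruitment, compares only age, sex and degree of hearing loss. The second comes at the 50% mark, once this share of "follow-up data is available to determine if a difference is evident in the outcomes. The results will guide the decision to continue the study". The section does not name the outcome, the visit, a threshold or the people who will see the comparison. The auditing section {23} sets an audit at the same milestone and again ties its results to continuation.

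Sample size {14} takes it that "a standardized difference of 0.6 was best for sample size estimation", and then "at a 5% significance level with a power of 80%, 45 patients will be required in each intervention arm", giving "90 participants in total at a randomization ratio of 1:1". A 50% dropout allowance raises this to 180. The interim look is not mentioned there.

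On oversight, section {21a} states that "A data monitoring committee is not needed over the course of this study" and gives low adverse-event risk as the reason. The steering group in section {5d} "will consist of PI, study co-ordinator, and a research assistant". Section {17a} says that audiologists and investigators are not blinded when outcomes are collected, and that the analysts receive data aggregated by arm.

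**The concern.** A between-arm outcome comparison that can influence whether a trial continues is part of its decision rule, so it changes the error rates. The sample-size section spends the whole 5% on one final test.

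The criterion can be read in two opposite ways. If an evident difference is a reason to stop and claim benefit, there are two chances of a false positive. If its absence is a reason to stop, a trial with a real effect may be closed when it has too few data to show it. The protocol does not say which is meant.

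The reason given for having no monitoring committee is about safety and does not address an efficacy look. No independent party is named to hold the comparison. The only governing group named is the one running the trial, and knowing the interim difference could influence the remaining recruitment and follow-up.

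**Working it through.** **Inputs.** Standardized difference 0.6, alpha 0.05, power 80%, 45 evaluable per arm, 50% dropout and 180 randomised, all from {14}. The trial is a superiority trial ({8}: "It has been designed to be a superiority trial"). Sidedness is not stated. Two-sided is assumed because it reproduces 45 per arm, whereas one-sided gives 35. The information fraction t at the look is assumed to be 0.5, with 0.25 to 0.75 as the range.

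**Step 1: reproduce the plan's figure.** The normal formula gives n = 2 × ((1.960 + 0.842)/0.6)² = 43.6, that is 44 per arm. Adding 1.96²/4 gives 44.6, that is 45. The exact t calculation gives power 79.5% at 44 and 80.4% at 45. With dropout, 90/(1 − 0.5) = 180. The stated size is therefore that of a single fixed-sample test with no allowance for a look.

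**Step 2: type I error if the trial may stop for benefit at p<0.05.** The interim and final statistics Z1 and Z2 have correlation √t. The overall error is 1 − P(|Z1|<1.96 and |Z2|<1.96).

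- t = 0.25: 9.1%
- t = 0.50: 8.3%
- t = 0.75: 7.3%

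Simulated t-tests agree for t = 0.5: 8.3% with 45 per arm at the end and 8.2% with 90 per arm.

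**Step 3: power under different readings of the criterion.** At 45 per arm the expected final Z is 0.6 × √(45/2) = 2.85. At t = 0.5 the expected interim Z is 2.85 × √0.5 = 2.01. The normal approximation is used throughout; with no look it gives 81.2%.

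| Rule at the look (t = 0.5) | Type I error | Power |
|---|---|---|
| Stop for benefit at p<0.05, else test at the end | 8.3% | 83.2% |
| Stop for futility only, if Z1<0 | 2.5% | 81.0% |
| Stop for futility only, if Z1<0.5 | 2.4% | 79.6% |
| Stop for futility only, if Z1<1 | 2.0% | 75.0% |
| Benefit at p<0.05, futility if Z1<1 | 6.2% | 77.0% |
| Continue only if p<0.05, then p<0.05 again at the end | 1.7% | 50% |
| Decide wholly on p<0.05 at the look | 5.0% | 52% |

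The last two rows are low because the chance of p<0.05 at the look is only about one half. It is 52% by the normal approximation and 50.3% by the exact t calculation with 22.5 per arm.

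**Step 4: what a preset boundary does.** At t = 0.5 and 45 per arm, normal approximation:

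| Boundary | Nominal p at look / end | Overall alpha | Power |
|---|---|---|---|
| O'Brien-Fleming-type spending | 0.003 / 0.049 | 0.050 | 81.1% |
| Classical O'Brien-Fleming | 0.0052 / 0.0480 | 0.050 | 80.9% |
| Pocock | 0.0294 / 0.0294 | 0.050 | 77.0% |

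**The case against.** Only a journal article is shown. A full protocol or analysis plan could hold a boundary and say who sees the split results, so it cannot be said that the trial has no boundary. That stands, and the point is confined to this text. But the article does more than stay silent: it states an outcome comparison, links it to continuation and words the criterion so that it can be read in opposite ways.

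Three stronger readings are tempting, and the document does not support them.

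- *That the look will decide continuation and is unblinded.* The text says that results guide the decision. Who sees them is not stated. Access by the trial team is an inference from the lack of a monitoring committee, the make-up of the steering group and the supply of data by arm.
- *That the 5% and the 80% definitely fail.* The rule is unknown, so the direction is too. Stopping only for benefit raises power to 83.2%. A futility-only look does not inflate type I error, and a mild one (Z1<0) leaves power at 81.0%. The failure modes pull in opposite directions and cannot be added together.
- *That power will be halved.* The figure of about 50% needs both an extreme rule and 22 to 23 completers per arm at the look. The trigger is half of the recruited participants' follow-up data. Half of 180 is 90, which could mean 45 per arm. With the planned 50% dropout that is the whole evaluable target, and power at the look would be 80.4%.

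A reader might also count several visits at each look and quote a much larger false-positive rate. Most of that excess comes from testing several time points, which is a separate matter.

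**Conclusion.** The concern holds in this limited form: the protocol ties continuation to a between-arm outcome comparison with an ambiguous criterion and no boundary in this document, while the sample size allows for one fixed test only. Neither the 5% nor the 80% is assured.

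The 8.3% (range 7.3% to 9.1%) rests on the assumption that the trial can stop and claim benefit at unadjusted two-sided p<0.05. The loss of power rests on the other reading and runs from negligible to about 30 percentage points, depending on the threshold and on how many completers there are at the look.

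The matter should be settled before the look takes place, because a rule written after the interim data are seen cannot protect the result. The trial status section reports recruitment under way since March 2021.

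**What to change.** Choose one of two routes and amend {21b} accordingly.

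1. Remove the between-arm outcome comparison. At the 50% milestone review only pooled recruitment, retention and data completeness. The fixed-sample calculation then stands as written.
2. Keep the look and preset its rule:
   - name a single primary comparison (one outcome, one visit or one summary over visits);
   - define the 50% point as a number of participants with that outcome observed;
   - fix one boundary, for example the O'Brien-Fleming-type spending boundary, two-sided p<0.003 at the look and p<0.049 at the end;
   - state that absence of a significant difference is not by itself a reason to stop;
   - have a statistician outside the trial team see the split results and report only continue or stop.

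The thresholds in route 2 apply at information fraction 0.5 and should be recomputed if the look falls elsewhere. If an analysis plan already contains such a rule, the protocol should cite it and bring the wording of {21b} into line.

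The cost is one paragraph through the amendment route in {25}. Route 2 lowers power from 81.2% to 81.1% and needs no material change to the sample size.

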### Methods for additional analyses (e.g., subgroup analyses) {20b}

There are no planned additional subgroup analyses.

### Methods in analysis to handle protocol non-adherence and any statistical methods to handle missing data {20c}

Sample population to be analyzed will be based on randomization. Any participant’s missing age data will be imputed with the mean of age of their allocation group. Missing sex data will not be analyzed. Participants without or with incomplete main outcome data including data-logged HA use hours and IOI-HA scores will be excluded from analysis.

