### Plans to promote participant retention and complete follow-up {18b}

A member from the audiology clinic will complete all forms along with participants to ensure the completeness of the forms. These standardized forms have been revised to improve understandability to ensure completeness. In the event of withdrawal prior to completion, any data collected up to the withdrawal time point will be retained and included for data analyses. A SPIRIT flow diagram demonstrates the data collection in the intervention and control groups (Table 2) [25].

**Table 2 Tab2:** Schedule of enrollment, interventions, and assessments

**Timepoint**	**Study period**											
	**Enrollment**		**Allocation**		**Post-allocation**				**Close-out**			
	***−t***_***1***_ −48 months to −1 day		***t***_***0***_ Day 0		***t***_***1***_ 1 month		***t***_***2***_ 3 months		***t***_***3***_ 6 months		***t***_***4***_ 12 months	
	**T**^**a**^	**C**^**b**^	**T**^**a**^	**C**^**b**^	**T**^**a**^	**C**^**b**^	**T**^**a**^	**C**^**b**^	**T**^**a**^	**C**^**b**^	**T**^**a**^	**C**^**b**^

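### The exclusion rule for incomplete outcome data conflicts with the promise to analyse data up to withdrawal, and on its natural reading gives a completers-only comparison under a plan that allows for 50% dropout

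*Protocol article*

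**What the plan says.** Three parts of the protocol article bear on this point.

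- **Missing data {20c}.** The section opens with "Sample population to be analyzed will be based on randomization" and closes with "Participants without or with incomplete main outcome data including data-logged HA use hours and IOI-HA scores will be excluded from analysis". The only imputation it describes is for age.
- **Retention {18b}.** For a participant who withdraws early, "any data collected up to the withdrawal time point will be retained and included for data analyses".
- **Sample size {14}.** "An allowance of 50% participant dropout rate was adopted in this study". In support, the section cites 20% dropout in the feasibility study and an earlier trial by the senior investigators, with 3 months' follow-up, which "resulted in 39.1% of participant data in the intervention arm being unavailable".

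Hours and IOI-HA are both collected at 1, 3, 6 and 12 months. Under Statistical methods {20a}, hours are compared between groups by independent-samples t-tests, and no repeated-measures model is named. Under Plans for assessment {18a}, the 1-month visit is labelled pre-intervention.

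**The concern.** An analyst cannot follow both sentences for a participant who attends at 1 and 3 months and then withdraws. The retention section puts that participant's hours into the analysis. The missing-data section, read naturally, removes the participant.

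If the exclusion rule prevails, membership of the analysed group is decided after randomisation. The outcome here is adherence to hearing aid use, and turning up for follow-up is a related behaviour, so people who stay may well differ in use from people who leave. The intervention arm also has an extra session with a therapist, so the reasons for staying could differ between arms. In that case the completers in the two arms are no longer comparable, and a difference in hours can arise without any effect of the intervention.

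The rule names hours and questionnaire scores together. A participant with full logged hours could therefore leave the primary analysis because a questionnaire is missing.

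**Working it through.** **1. The plan's own figures.** Inputs from Sample size {14}: "a standardized difference of 0.6 was best for sample size estimation", and "at a 5% significance level with a power of 80%, 45 patients will be required in each intervention arm". A two-sided t-test at 5% with 80% power and a difference of 0.6 SD needs 44.6, rounded up to 45 per arm. Then 90/(1 − 0.5) = 180. Both stated figures reproduce. At the planned loss, 45 per arm remain, with power of about 80%.

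**2. The sentences applied to cases.**

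| Participant | Retention {18b} | Missing data {20c}, natural reading |
|---|---|---|
| Attends months 1 and 3, then withdraws | Data analysed | Excluded |
| Full hours, one questionnaire missing | Not addressed | Excluded |

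**3. What selection can do.** This step takes no true effect, a normally distributed outcome and 50% retained in each arm. The mean shift among those retained is ρ × φ(z)/retention, where ρ is the correlation of retention with the outcome. At 50%, φ(0)/0.5 = 0.399/0.5 = 0.798. The bias in the arm difference is the between-arm difference in ρ times 0.798. The SE is √(2/45) = 0.211. The differences in ρ are assumed.

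| Difference in ρ | Bias (SD) | Two-sided type I error (nominal 5%) |
|---|---|---|
| 0.1 | 0.08 | about 7% |
| 0.2 | 0.16 | about 12% |
| 0.3 | 0.24 | about 21% |
| 0.5 | 0.40 | about 47% |

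For the third row: 0.24/0.211 = 1.14, and 1 − Φ(1.96 − 1.14) is about 0.21. At 39.1% loss the bias over the same range is 0.06 to 0.32 SD. At 20% loss it is 0.04 to 0.18 SD.

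**4. Comparison of methods by simulation.** Assumptions: 90 per arm, SD 1, correlation 0.7 between visits, no true effect, all 1-month hours observed, and monotone loss of about 28%, 16% and 16% at months 3, 6 and 12. Retention is then 0.72 × 0.84 × 0.84 = 0.508. Control-arm loss depends on the last observed hours and intervention-arm loss does not. The table gives the bias in the 3-month difference (intervention minus control). Ranges reflect different calibrations of the dropout model.

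| Analysis | Log-odds 0.5 per SD | Log-odds 1.0 per SD |
|---|---|---|
| Completers, unadjusted | −0.21 to −0.22 | −0.35 to −0.41 |
| Completers, adjusted for 1-month hours | −0.05 to −0.06 | −0.09 to −0.10 |
| Available cases at 3 months, unadjusted | −0.09 to −0.10 | −0.16 to −0.17 |
| All available, adjusted for 1-month hours | 0.00 | 0.00 |

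With equal selection in both arms, every row is 0.00.

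**5. Precision under random loss.** At 3 months, 90 × 0.72 = 64.8 per arm are observed. Completers number 90 × 0.508 = 45.7. Adjustment leaves residual variance 1 − 0.7² = 0.51.

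- Completers, unadjusted: √(2/45.7) = 0.21
- Completers, adjusted: √(0.51 × 2/45.7) = 0.15
- All data, adjusted: √(0.51 × 2/64.8) = 0.13

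**The case against.** The rule does not say what triggers exclusion. Since hours are compared by t-tests with no repeated-measures model, and the retention section keeps data up to withdrawal, one can read it as available-case: a participant without 12-month hours leaves the 12-month test only. That reading is possible and would remove the contradiction. The text does not state it, however, and under one-arm selection it still carries a bias of about 0.1 to 0.17 SD at 3 months.

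A reader might infer a second contradiction, between the opening and closing sentences of the missing-data section. The documents do not support this firmly. Under a heading on non-adherence, the opening sentence can simply mean analysis by allocated arm.

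A reader might also infer that half the sample will be lost. The 50% is a planning allowance, and the cited rates are 20% and 39.1%. The 39.1% includes questionnaires not fully completed, so it is not all loss of hours. Nor should missingness be compounded as if hours and questionnaire were independent: both are collected at the same visits, staff complete forms with participants, and missed visits prompt a telephone call.

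Finally, the largest bias, 0.4 SD or two thirds of the 0.6 target, needs the strictest reading, no covariate and selection in one arm only. The documents give no evidence of one-arm selection. Adjusting the completers for 1-month hours removes about three quarters of the bias, and about 70% of the SE gain from 0.21 to 0.13 also comes from that covariate. In the simulation the bias also runs against the intervention. The all-data estimate is unbiased there by construction, because loss was generated from observed hours. All of this stands, and it limits the size of the problem. It does not rescue the rule as written.

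**Conclusion.** The rule is wrong as written and should be changed before analysis. What is secure is that the missing-data and retention sections conflict on the natural reading, and leave the analysis set undefined on the kindest one. A completers-only comparison would discard valid post-randomisation hours, tie the primary outcome to a separate questionnaire, and open the comparison to selection bias that enlarging the trial to 180 cannot correct.

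The size of the bias is not known. On assumed one-arm selection with about 50% loss it is about 0.2 to 0.4 SD for unadjusted completers, and it is zero if selection is the same in both arms. These figures illustrate what the rule permits and do not predict the result. The sample size calculation itself is sound.

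**What to change.** Replace the exclusion sentence in Missing data {20c} and align it with Retention {18b}:

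- Analyse all randomised participants in their allocated arm, using every observed hours value.
- Use a method valid under missing at random. A mixed model for repeated measures that uses the pre-intervention 1-month hours would do, as would multiple imputation. The choice between them is secondary. If 1-month hours serve as a covariate, reconcile this with the Outcomes section, which lists 1 month among the post-intervention time points.
- Never drop an hours value because the IOI-HA is missing, or the reverse.
- Keep the complete-case result as a sensitivity analysis, and add one analysis under missing not at random, for example a delta adjustment.

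The cost is protocol wording, slightly more analysis work and reliance on a missing-at-random assumption, which the last item probes. No new data are needed, and 45 per arm and 180 in total stand.

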### Plans to give access to the full protocol, participant-level data, and statistical code {31c}

The full protocol will be available for public access. Participant-level dataset and statistical code will not be available for public access.

## Oversight and monitoring

### Composition of the coordinating center and trial steering committee {5d}

The coordinating center and trial steering group (TSC) will consist of PI, study co-ordinator, and a research assistant.

### Composition of the data monitoring committee, its role, and reporting structure {21a}

A data monitoring committee is not needed over the course of this study as there is a low risk of adverse events.

### Adverse event reporting and harms {22}

After participants have provided consent and enrolled in the study, adverse events will be collected and recorded until the end of the study period. Adverse events that occur after consent is signed, but before receiving the study intervention will be reported as not related to our intervention. Any serious adverse event that occurs will be reported to the institutional review board (IRB) and will be documented.

### Frequency and plans for auditing trial conduct {23}

Study-related monitoring, audits, and inspections by the clinical research ethics board of all study-related documents will be performed when 30% of participant recruitment is achieved. The PI will also ensure the legitimacy and capability for inspections of facilities. A second audit will be performed when 50% of the recruited participants’ follow-up data is available. The results will guide the decision to continue the study.

### Plans for communicating important protocol amendments to relevant parties (e.g., trial participants, ethical committees) {25}

Any modifications to the protocol including changes in study objectives, study design, participants, sample size, or study procedures will require a formal amendment to the protocol and approval by the IRB prior to implementation.

### Dissemination plans {31a}

The PI will have access to the data sets. The results of this trial will be disseminated to the public through peer-reviewed research publications, conference abstracts, meeting presentations, posters, and social media. The study will report results based on the Consolidated Standards of Reporting Trials guidelines.

